**Fig 1 pone.0285823.g001:**
[figure not shown]
Schedule of enrolment, interventions, and follow-up of the FinnTrunk study. The specific time points are listed in the columns and the events are given in the rows. Participants will be randomly allocated to EVLA without (x^1^) or with (x^2^) concomitant UGFS before procedure at the treatment visit. All participants will have a follow-up visit at 3 months, 1 year, 3 years, and 5 years. If found necessary, the varicose tributaries can be treated at any of the follow-up visits. Abbreviations: the Aberdeen Varicose Vein Questionnaire (AVVQ), (the clinical class of) the Clinical-Etiology-Anatomy-Pathophysiology classification (CEAP), endovenous laser ablation (EVLA), Duplex ultrasound (DUS), EuroQoL quality of life questionnaire (EQ-5D-5L), patient related outcome measures (PROMs), ultrasound-guided foam sclerotherapy (UGFS), the Venous Clinical Severity Score (VCSS), the Venous Disability Score (VDS). ^1^According to the randomized allocation (group 1) ^2^According to the randomized allocation (group 2) *If judged necessary by the patient (both groups).

## Statistical analysis

The sample size calculation for the study was based on the systematic review and meta-analysis by Aherne et al. [13]. Combined treatment of the saphenous trunk and varicose tributaries results in a 6.3% and staged treatment in a 36.1% reintervention rate. According to the power analysis, statistical dichotomous analyses between two independent groups with an alpha of 0.01, and a power of 80%, thus a 1:1 randomization would result in a sample size of 84. When calculated for a 12% difference, the anticipated sample size would, accordingly, be 228. Considering the long follow-up (5 years) and the anticipated large number of dropouts, the sample size was set at 260 (130 for each group).

For dropouts, the results will be analyzed until their last follow-up visit. If a patient has not completed their treatment or has not been treated according to their allocation (crossover), their participation in the study will be terminated and their data will not be included in the analysis.

All statistical analyses will be performed using SPSS version 27 for Mac (IBM, Armonk, NY, USA). Descriptive statistics will be used to summarize patient baseline characteristics. Mean values and standard deviations (SD) will be applied for continuous variables if normally distributed. Correspondingly, median values and interquartile range (IQR) will be applied for non-parametric variables. The Fisher’s exact test will be used to compare categorical variables, and the Wilcoxon Signed-Rank Test and the Mann-Whitney U test will be used to compare ordinal variables. Normally distributed continuous variables will be compared by using the Student’s t-test for values previously tested using the Shapiro–Wilk test. A *p*-value of < .05 will be considered statistically significant.

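### The 228 given for a 12-point difference does not follow from alpha 0.01 and 80% power if the 12 points start at the protocol's 6.3%, and the planning alpha differs from the analysis threshold

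*Protocol article*

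**What the plan says.** All of the text is in the Statistical analysis section of the protocol article.

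- Rates taken from a cited meta-analysis: combined treatment "results in a 6.3% and staged treatment in a 36.1% reintervention rate".
- Planning level and power: "statistical dichotomous analyses between two independent groups with an alpha of 0.01, and a power of 80" per cent. Sidedness is not stated.
- First result: "thus a 1:1 randomization would result in a sample size of 84".
- Second result: "When calculated for a 12% difference, the anticipated sample size would, accordingly, be 228". No new alpha or power is named, and the two rates that differ by 12 points are not given.
- The target is then set at 260, 130 per group, to allow for dropouts over five years.
- Categorical variables are to be compared with Fisher's exact test.
- Analysis threshold: a p-value "value of < .05 will be considered statistically significant".

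**The concern.** The link word in the second result carries alpha 0.01 and 80% power over from the sentence before it. A reader will take it that 228 patients give 80% power for a 12-point difference at alpha 0.01, and that 260 keeps this with a margin for dropout. The enrolment target rests on that sentence.

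Two things do not fit. On the only combined-arm rate that the document gives, 228 is far too small for alpha 0.01. And the section plans at 0.01 but tests at .05 without saying why. At stake is whether the stated power can be relied on, and which significance level the primary comparison was designed for.

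**Working it through.** **Inputs.** From the Statistical analysis section: 6.3% and 36.1%; alpha 0.01; power 80%; 1:1 allocation; totals 84, 228 and 260; threshold p < .05. Assumed, because not stated: two-sided tests, and a 12-point difference that starts at 6.3%, so 6.3% versus 18.3%.

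**Formulas, per group.** With d = p2 − p1, q = 1 − p and p̄ the mean of the two rates:

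- Unpooled: n = (zα + zβ)² (p1q1 + p2q2) / d²
- Pooled: n = [zα√(2p̄q̄) + zβ√(p1q1 + p2q2)]² / d²

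Here zα = 2.576 (two-sided 0.01) or 1.960 (two-sided 0.05), and zβ = 0.842. So (zα + zβ)² is 11.679 or 7.849.

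**Step 1: reproduce 84 (6.3% versus 36.1%).** p1q1 + p2q2 = 0.0590 + 0.2307 = 0.2897; d² = 0.0888.

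| Two-sided alpha | Unpooled, per group | Pooled, per group | Total, rounded up per group |
|---|---|---|---|
| 0.01 | 38.1 | 42.5 | 78 to 86 |
| 0.05 | 25.6 | 28.3 | 52 to 58 |

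The stated 84 fits alpha 0.01 with the pooled formula: 2 × 42.46 = 84.9, which is 84 rounded down and 86 rounded up per group. It does not fit alpha 0.05 at 80% power.

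**Step 2: try 228 (6.3% versus 18.3%).** p1q1 + p2q2 = 0.0590 + 0.1495 = 0.2085; d² = 0.0144; ratio 14.482.

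- Alpha 0.01, unpooled: 11.679 × 14.482 = 169.1, so 170 per group, 340 in total. Pooled: 173.5, so 174 per group, 348 in total.
- Alpha 0.05, unpooled: 7.849 × 14.482 = 113.7, so 114 per group, 228 in total. Pooled: 116.4, so 117 per group, 234 in total.
- One-sided alpha 0.01: 292 (unpooled) to 300 (pooled).

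Continuity-corrected and arcsine versions widen the two-sided 0.01 range to 330 to 380. None of these reaches 228 at alpha 0.01.

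**Step 3: other starting rates.**

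| Rates | Two-sided alpha | Formula | Result |
|---|---|---|---|
| 2% vs 14% | 0.01 | unpooled | 228 total |
| 6% vs 18% | 0.05 | pooled | 228 total |
| 24.1% vs 36.1% | 0.05 | pooled | 228.2 per group, 458 total |

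The first needs a rate that appears nowhere in the document. The second is 6.3% rounded. The third starts from the document's 36.1% and gives 228 as a number per group.

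**Step 4: power for 6.3% versus 18.3%.** Power = Φ{[d√n − zα√(2p̄q̄)] / √(p1q1 + p2q2)}, with √(2p̄q̄) = 0.4645 and √0.2085 = 0.4567. For n = 114 at alpha 0.01: (1.2813 − 1.1964) / 0.4567 = 0.186, so Φ = 0.574. The remaining cells follow in the same way. Exact Fisher power was found by summing over all outcome tables.

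| Total | Alpha 0.01, normal | Alpha 0.01, Fisher | Alpha 0.05, normal | Alpha 0.05, Fisher |
|---|---|---|---|---|
| 228 | 57% | 53% | 79% | 74% |
| 260 | 65% | 59% | 84% | 81% |

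All values are before dropout.

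**The case against.** The strongest case for the plan has four parts.

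- **The starting rate is the reviewer's.** The document says only that the difference is 12%. This stands: 6.3% versus 18.3% is an assumption, and 2% versus 14% would give 228 at the stated alpha. A reader might infer that 228 can arise only from 6.3%; step 3 shows that it cannot be put that way. Still, a 2% rate has no basis in the text, while 6.3% does.
- **No single formula tried gives both totals.** 84 fits the pooled formula at alpha 0.01, and 228 fits the unpooled formula at alpha 0.05. With the unpooled formula, alpha 0.05 and 95% power, the first scenario also comes to 84.8. This stands too. That the two totals rest on different alphas is a well-supported inference, not something the document shows. The match does not depend on the choice of formula, though: pooled gives 234 at 0.05, within 3% of 228, and 348 at 0.01.
- **Only one decision rule is written, p < .05.** A reader might infer that a primary p-value between .01 and .05 would count as significant under one sentence and not under another. The document does not support that, because alpha 0.01 appears only as a planning input. Planning at a stricter level than the test is conservative in itself. What remains is that the section gives two levels and no reason.
- **The trial may be adequately powered.** At .05, 260 patients give 81 to 84% for 6.3% versus 18.3% before dropout, and for the cited 6.3% versus 36.1% power exceeds 99.9% even at alpha 0.01. This stands and limits the harm.

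**Conclusion.** The point holds as a defect in the stated basis of the sample size. On the protocol's own 6.3%, and two-sided, 228 does not follow from alpha 0.01 and 80% power: 340 to 348 would be needed, about 50% more. The figure 228 agrees with alpha 0.05, and 84 agrees with alpha 0.01, yet the paragraph presents them as one calculation.

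A reader might go further and infer that the trial is underpowered. The documents do not support that as a general statement. It would be so for 6.3% versus 18.3% if alpha 0.01 governed the primary test, which the analysis text does not say. Nor can it be concluded that the 12 points sit at 24.1% versus 36.1%. That pair matters only because it makes it necessary to say whether 228 is a total.

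The conclusion rests on the assumed starting rate of 6.3%. The choice between one and two sides does not change it, since one-sided alpha 0.01 still needs 292 to 300. Type I error at .05 and the conduct of the trial are unaffected. It should be fixed, but it does not put the trial in doubt.

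**What to change.** Restate the calculation from the inputs actually used; the sponsor should not simply adopt the rates that happen to reproduce 228.

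1. Name one alpha, with its sidedness, for the primary test, and use it in both the sample size paragraph and the analysis paragraph.
2. Give the two rates and the formula behind the 12-point figure, and confirm that 228 is a total and not a number per group.
3. Correct whichever figure does not follow.
   - If alpha 0.05 governs: label 228 as an alpha 0.05 figure, and either label 84 as an alpha 0.01 figure or recompute it (52 to 58).
   - If alpha 0.01 governs: say so in the analysis text, and restate power at 260 as about 59 to 65% for 6.3% versus 18.3%, before dropout.

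The cost is about two sentences of text. Nobody more is enrolled and nothing in the conduct changes. The price is that the statement on the 12-point difference becomes less favourable: either a less strict alpha or a power below 80%.

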## Methods

### Study design and data management

The FinnTrunk study is a non-blinded, multicenter, parallel-group, randomized, controlled study, which will be conducted in four large Finnish hospitals (Helsinki University Hospital, Oulu University Hospital, Satasairaala hospital in Pori, and Turku University Hospital). The participating hospitals were selected based on the high volume of endovenous procedures in their respective vascular surgery units. Data will be collected by study investigators at each participating center and uploaded to an electronic data capture system (REDCap, Vanderbilt University, Nashville, TN, USA) hosted by and at Helsinki University Hospital. The FinnTrunk study was registered on ClinicalTrials.gov on 24 February 2021 (study identifier NCT04774939), and the first patient was entered in the study register on 6 October 2021. The first study results will be published in a peer-reviewed journal in 2024.

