### Patient enrolment and randomization

The patients who fulfill the study criteria will be given a brief information letter and offered the possibility to participate in the study. The baseline characteristics of the patients who give their written informed consent will be recorded in the study register. The patients will fill in the Aberdeen Varicose Vein Questionnaire (AVVQ) [27] (with question 1 omitted [28, 29]) and the EQ-5D-5L, while the investigator will ascertain and record the patient’s Venous Clinical Severity Score (VCSS) [21], Venous Disability Score (VDS) [30], and the clinical class of the Clinical-Etiology-Anatomy-Pathophysiology (CEAP) classification [20], in addition to recording the location and extent of the varicose tributaries.

The patients will be randomly allocated with the REDCap to one of the two study groups before the procedure. Patients in group one will be treated with EVLA of the incompetent saphenous trunk without treatment of the varicose tributaries. Patients in group two will be treated with UGFS of the varicose tributaries concomitantly with the EVLA.

If the patient wishes to decline participation in the study, they will be treated according to the usual regime of the unit.

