### Outcome measures and follow-up

The duration of the follow-up will be five years. The primary outcome measure will be the need for additional treatment of the varicose tributaries during the follow-up, as judged by the patient. The secondary outcome measures will be the cost of treatment and recurrence of varicose disease. Other outcome measures of interest will the length of the procedure time and the impact of treatment on the Aberdeen Varicose Vein Questionnaire (AVVQ) score, the Venous Clinical Severity Score (VCSS), health-related quality of life (the EuroQoL EQ-5D-5L) score, and patient-related outcome measures (PROMs). Data pertaining to PROMs will be collected at 1 year with two questions: “Was the treatment you were given of good quality?” and “Did the treatment you were given meet your expectations?”

In addition, the following data will be collected at the 3-month follow-up visit: pain score based on numeric rating scale (NRS) during the procedure and at three time points post-procedure, the use of analgesics, and the possible procedure-related complications. Patients will also be asked about the duration of sick leave and for their estimate of the appropriate recovery time.

The study leg will be assessed using DUS at each follow-up visit. The protocol for the examination will be identical with the diagnostic DUS described previously under Study setting and patient screening, i.e., the diameter of GSV and SSV will be measured and both veins will be assessed for patency and reflux regardless of whether the vein has been treated or not; the AASV will be systematically assessed only when it has been the target for ablation. Apart from that, it will be assessed as needed, i.e., if there are varicose tributaries that could be connected to the AASV. The treated saphenous trunk will be assessed according to the recommendations and definitions of De Maeseneer et al. [23]. Data on the saphenous trunks and varicose tributaries will be recorded in the study register. During the follow-up visits, patients in both study groups will be able to receive UGFS, if judged necessary by the patient, for the remaining or new tributaries. The additional treatments will be recorded in the study register.

A schematic diagram of the timeline of the study [31] is presented in Fig 1.

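### Randomized patients who cross over or do not complete treatment are taken off study and out of the analysis, which can bias the comparison in either direction and cannot be undone later

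*Protocol article*

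**What the plan says.** The protocol article, Statistical analysis, sets two rules for patients who depart from the plan.

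- Dropouts: "For dropouts, the results will be analyzed until their last follow-up visit".
- Crossover or incomplete treatment: for anyone who did not finish treatment, or who received something other than what was allocated, "their participation in the study will be terminated and their data will not be included in the analysis".

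The second rule is stated for the analysis as a whole. The article does not name an as-allocated analysis or confine the exclusion to a secondary one.

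Three other places bear on it:

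- Patient enrolment and randomization: "The patients will be randomly allocated with the REDCap to one of the two study groups before the procedure".
- Study design and data management: "The FinnTrunk study is a non-blinded, multicenter, parallel-group, randomized, controlled study".
- Outcome measures and follow-up: "The primary outcome measure will be the need for additional treatment of the varicose tributaries during the follow-up, as judged by the patient".

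The Fig 1 caption says that all participants attend at 3 months, 1 year, 3 years and 5 years.

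**The concern.** Randomization makes the two groups comparable as allocated. A rule that drops patients for what happened at or after the procedure keeps that comparability only if those dropped are like those kept, or are dropped alike in both arms. Neither can be presumed here. Group 1 has to complete laser ablation alone, while group 2 has to complete ablation plus foam, so departures can differ in number and kind. The extent of the tributaries could influence both a departure at the procedure and the later wish for treatment. Operator and patient know the allocation, and the patient decides whether further treatment is needed.

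The stated aim is to compare two treatment strategies, and a failed or altered procedure is part of what a strategy delivers, including its cost, which is a secondary outcome. Ending participation is worse than leaving a patient out of one analysis: the 3-month complication data and all later outcomes are never collected, so no later analysis plan can restore them.

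**Working it through.** **What the plan supplies.** It gives no crossover or non-completion rate and no reasons for departures. The usable figures are event rates of 6.3% (combined) and 36.1% (staged), 130 patients per group, and a 0.05 significance level, all from Statistical analysis.

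**Reproducing the plan's own figure.** For 6.3% against 36.1%, two-sided alpha 0.01, power 80%, mean rate 0.212:

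n per arm = [2.576·√(2·0.212·0.788) + 0.842·√(0.063·0.937 + 0.361·0.639)]² / 0.298² = 42.5, so 43 per arm and 86 in total, against the stated 84. The rates are being read as intended. The present point does not depend on this figure.

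**Bias formula.** Let p be an arm's true event rate, q the fraction excluded from it, and r the event rate among those excluded. The rate among those kept is (p − q·r)/(1 − q), so the shift is q·(p − r)/(1 − q). Its sign is that of p − r. Excluding high-risk patients lowers an arm's rate, excluding low-risk patients raises it, and r = p gives no shift.

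**Illustration with no true difference.** Assume the same true rate in both arms, exclusions from one arm only, and r = 2p. For p = 0.361 and q = 0.10:

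- rate kept = (0.361 − 0.0722)/0.90 = 0.321, false difference d = 0.040;
- n = 117 and 130, pooled rate 0.342, null standard error se0 = 0.0605, actual standard error se1 = 0.0603;
- rejection probability = Φ((0.040 − 1.96·0.0605)/0.0603) + Φ((−0.040 − 1.96·0.0605)/0.0603) = 0.101.

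| True rate, both arms | Excluded from one arm | Rate among those kept | False difference (points) | Error rate, nominal 5% |
|---|---|---|---|---|
| 36.1% | 5% | 34.2% | 1.9 | 6.1% |
| 36.1% | 10% | 32.1% | 4.0 | 10.1% |
| 36.1% | 15% | 29.7% | 6.4 | 18.0% |
| 20% (assumed) | 5% | 18.9% | 1.1 | 5.5% |
| 20% (assumed) | 10% | 17.8% | 2.2 | 7.2% |
| 20% (assumed) | 15% | 16.5% | 3.5 | 10.7% |

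With r = 1.5p the error rate runs from 5.1% to 8.1% over the same cases. These are normal approximations. The planned Fisher test is conservative, so its error rates would be somewhat lower.

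**Both directions are possible.** Excluding 10% of group 2 at twice its 6.3% risk gives (0.063 − 0.0126)/0.90 = 5.6%, which widens a true difference by 0.7 points. The same kind of exclusion in group 1 narrows it.

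**Precision only.** If exclusions carry average risk and fall equally on both arms, power for 6.3% against 18.3% (a 12-point difference; this base rate is assumed) at two-sided 0.05 falls from 84.2% with 130 per arm to 82.4%, 80.2% or 77.7% when 5%, 10% or 15% are lost. The allowance for losses is 260 − 228 = 32 patients.

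**The case against.** The best reply is that the effect may be small. Allocation takes place at the treatment visit itself, which leaves little time to depart from it. Connected tributaries are an inclusion criterion, so group 2 patients should have something to treat. Group 1 patients can have foam from the 3-month visit, which eases pressure to cross over. At 5% excluded with twice the risk, the error rate moves only to 6.1%. All of this stands as an argument about size. It does not make the rule sound.

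A reader might infer that the exclusions shrink the difference and make stand-alone ablation look more adequate than it is, and that analysis as allocated would restore the lost effect. The document supports neither. Assume true rates of 18.3% and 6.3%, a fraction q of group 1 foamed at the index procedure, need r among them had they not been foamed, and the plan's 6.3% combined-treatment rate once foamed. The differences from group 2 are then (0.183 − q·r)/(1 − q) − 0.063 with exclusion and (0.183 − q·r + q·0.063) − 0.063 as allocated:

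| q | r | With exclusion (points) | As allocated (points) |
|---|---|---|---|
| 5% | 40% | 10.9 | 10.3 |
| 5% | 80% | 8.8 | 8.3 |
| 10% | 40% | 9.6 | 8.6 |
| 10% | 80% | 5.1 | 4.6 |

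On these inputs the as-allocated difference is the smaller one, and neither returns to 12. If index foaming in group 1 were instead counted as an event, the last row would become 0.183 − 0.08 + 0.10 − 0.063 = 14.0 points. The counting rule therefore matters as much as the analysis set.

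Two further overstatements should be avoided. Immediate complications are entered in the register at the procedure, so not all safety data are lost. And the analysed set is not purely per-protocol, since dropouts contribute up to their last visit.

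**Conclusion.** The point holds as a defect of design. The plan's only stated rule removes randomized patients for events after allocation, in an open trial with a patient-judged outcome, and stops their follow-up. It can bias the comparison in either direction, it conflicts with the visit schedule in the Fig 1 caption, and the loss is irreversible.

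Size and direction cannot be derived from the document. The increase in error rate from 5% to about 10% rests wholly on the assumed 10% one-sided exclusion at twice the average risk. The claim that the rule favours either strategy is not established.

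**What to change.** Replace the sentence on crossover and incomplete treatment with wording such as:

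> All randomized patients are followed at every scheduled visit and analysed in their allocated group, whatever treatment they received. Excluding patients with incomplete treatment or crossover is a sensitivity analysis only. Deviations are reported by arm with reasons.

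Add two definitions:

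- Foam sclerotherapy given to group 1 at a follow-up visit belongs to the staged strategy and is not a crossover.
- Tributary treatment of a group 1 patient at the index procedure is counted in the primary outcome in a prespecified way, for example as an event, with the alternative as a sensitivity analysis.

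The planned 260 patients do not change. The cost is protocol wording and continued routine follow-up of patients who have already consented, probably few. Crossovers may dilute the contrast, and the sensitivity analyses would show how far the result depends on them.

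### Tributary extent is recorded at baseline and bears directly on the primary outcome, but no named between-group test uses it: a valid analysis that gives up a modest amount of power

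*Protocol article*

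**What the plan says.** The section on enrolment and randomization lists the baseline questionnaires and scores, "in addition to recording the location and extent of the varicose tributaries". It then states: "The patients will be randomly allocated with the REDCap to one of the two study groups before the procedure". The Fig 1 legend places allocation at the treatment visit. Extent is therefore collected before the arm is known.

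Under Outcome measures and follow-up: "The primary outcome measure will be the need for additional treatment of the varicose tributaries during the follow-up, as judged by the patient".

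The Statistical analysis section sizes the trial as a dichotomous comparison of two independent groups. It names methods by type of variable: "The Fisher’s exact test will be used to compare categorical variables", "the Wilcoxon Signed-Rank Test and the Mann-Whitney U test will be used to compare ordinal variables", and Student's t-test for normally distributed continuous variables. The only stated use of baseline data is this: "Descriptive statistics will be used to summarize patient baseline characteristics". No regression model appears. No test is tied to the primary outcome by name; Fisher's test follows because the outcome is categorical.

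**The concern.** Baseline extent is a natural candidate predictor of this outcome. In group 1 the tributaries recorded at entry are left untreated, and the endpoint asks whether those or new ones later need treatment. If extent predicts the outcome, an unadjusted comparison counts predictable differences between patients as noise. The estimated risk difference is then less precise than it could be, and a chance difference in extent between arms stays in the estimate. The article describes no balancing of the allocation on extent. It also expects many dropouts over five years, so there is little power to spare in the smaller, 12-point scenario.

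**Working it through.** **Inputs from the article.** "Combined treatment of the saphenous trunk and varicose tributaries results in a 6.3% and staged treatment in a 36.1% reintervention rate"; sample size calculated "with an alpha of 0.01, and a power of 80"%; 84 patients in total for those rates; 228 for a 12% difference; 260 adopted (130 per group); significance threshold .05 in the analysis.

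**Inputs assumed.** The article gives neither the base rate for the 12-point scenario nor the prognostic strength of extent. I take 6.3% vs 18.3%, and treat extent as one standardised continuous score with an odds ratio (OR) of 1.5 to 4.5 per SD.

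**1. The plan's own figures.**
- For 6.3% vs 36.1%, two-sided 0.01, 80% power, pooled formula: n per arm = [2.576·√(2·0.212·0.788) + 0.842·√(0.063·0.937 + 0.361·0.639)]² / 0.298² ≈ 42.5. That rounds up to 43, or 86 in total, close to the stated 84.
- For 6.3% vs 18.3%, two-sided 0.05, unpooled formula: (1.960 + 0.842)²·(0.063·0.937 + 0.183·0.817) / 0.12² ≈ 113.7. That rounds up to 114, or 228 in total, which matches the stated figure.
- At two-sided 0.01 the same 12-point scenario needs 348 (pooled). The check below therefore uses 0.05. The mismatch between the two alphas is a separate matter.

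**2. The test as named.** Exact power of Fisher's test at 6.3% vs 18.3%, two-sided 0.05, is 74% with 114 per arm and 81% with 130 per arm.

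**3. What the covariate adds.** Trials were simulated with marginal risks held at 6.3% and 18.3%. The comparison is a pooled chi-square test against the risk difference standardised from a logistic regression on group and score, with an influence-function standard error. Each cell gives unadjusted → adjusted power, in %.

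| OR per SD (approx. correlation with outcome) | 114 per arm | 130 per arm | 114 per arm, half the slope in group 2 |
|---|---|---|---|
| 2 (0.21) | 80.6 → 82.9 | 85.6 → 87.8 | 80.6 → 82.0 |
| 2.7 (0.28) | 80.9 → 85.5 | 85.9 → 89.3 | 81.4 → 84.2 |
| 4.5 (0.37) | 80.3 → 88.6 | 85.8 → 92.0 | 82.0 → 86.9 |

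Monte Carlo error is about 1 point; a repeat at 2.7 per SD with 114 per arm gave 80 → 84. At 1.5 per SD, logistic likelihood-ratio tests without and with the covariate had 83% and 84% power. The covariate's own contribution is thus about 1 to 4 points for ORs of 1.5 to 2.7, and about 6 to 9 points at 4.5. Type I error of the adjusted analysis was 4.8% to 5.6%.

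**4. Separating the two sources of gain.** At 114 per arm, going from Fisher (74%) to the adjusted analysis at 2 per SD (82.9%) gains about 9 points. About 80.6 − 74 = 6.6 of these come from leaving Fisher's conservative test, and 82.9 − 80.6 = 2.3 from the covariate.

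**5. At the cited rates.** For 6.3% vs 36.1%, Fisher's exact power at two-sided 0.05 is above 99.9% with 114 per arm and 98.9% with only 65 per arm. Adjustment has almost nothing to add there.

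**6. Events available.** 130·0.063 + 130·0.183 = 8.2 + 23.8, or about 32.

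**The case against.** **Left to an unseen analysis plan.** Choice of covariates is commonly settled there, and the tests are listed generically by variable type. This stands in part: nothing in the article rules out an adjusted model, and a reader should not infer that none is planned. But the article is not silent. It names its tests, and the comment addresses that stated choice.

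**No error is involved.** This stands. Randomisation keeps the unadjusted test valid; under the null, Fisher's rejection rate was 2.6% to 3.9% at a nominal 5%. A reader might infer that imbalance in extent would bias the result. It would not: chance imbalance is ordinary sampling variation, already covered by the test's error rate. The loss is one of efficiency.

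**Prognostic strength is unknown.** This also stands. The article never calls extent prognostic. All patients must have tributaries connected to the trunk, and most are C2–C3, which narrows the range. Need is judged by the patient, and the Introduction notes that symptom relief from truncal ablation may leave some patients not wanting more treatment. In group 2 the tributaries have already been treated, so prediction may be weaker. These points argue for the lower part of the range, not for zero.

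**A larger gain is tempting.** With a correlation of 0.5, Φ[(1.96 + 0.842)/√(1 − 0.25) − 1.96] gives 90% power against 80%. That is unrealistic for so infrequent a binary outcome: even an OR of 12 per SD gives correlations of only 0.40 and 0.55 in the two arms.

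**Conclusion.** The point holds as a modest loss of efficiency. Baseline extent is recorded before allocation and relates directly to the primary outcome, yet no named comparison uses it. If 6.3% vs 18.3% applies, at two-sided 0.05 with 114 to 130 per arm, adjustment adds about 1 to 4 points of power for ORs of 1.5 to 2.7 per SD and about 6 to 9 at 4.5. With half the slope in group 2 and 114 per arm, the gains at 2, 2.7 and 4.5 per SD are about 1, 3 and 5 points. At the cited 6.3% vs 36.1% the gain is negligible. The base rate and the prognostic strength are both assumptions.

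A reader might go further and say that prognostic information is thrown away. The documents do not support that: the data are kept and summarised, and their prognostic value is not reported.

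**What to change.** In the Statistical analysis section, state that the primary between-group comparison is the risk difference standardised from a logistic regression of the primary outcome on treatment group and one baseline extent score, with a robust (influence-function) or bootstrap standard error. Build the score from the location and extent data already recorded, and fix its definition before outcome data are examined. Standardise over the trial's primary analysis population; who belongs in that population is a separate question that this change need not settle. Report the unadjusted test as supportive. If the outcome is analysed as time to first need, enter the same score in that model.

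The cost is small: a short addition to the text and slightly more analysis, with no new data, visits or patients. The article describes no ready-made extent score, so one must be defined and justified in advance. With about 32 expected events, the model should hold only one or two baseline terms.
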